#### Secondary outcomes

*Protocol compliance and adherence* to treatment schedule between active rTMS and sham control groups, comparing proportion of protocol-compliant and non-protocol compliant participants overall and separated by intervention group.*Blinding success* will be measured by asking participants which intervention they believe they received (real, placebo or unsure) immediately after the first intervention, after their 10th session, and after the final intervention. A visual analogue scale (VAS) will also be used to measure how certain participants feel about their selection of intervention group. Number and percentage of participants’ selections will be presented in a table, separated by intervention group.*MRI* data will be evaluated from scans collected at baseline (up to 2 weeks prior to the first intervention visit) and post-intervention (within 2 weeks of the last intervention visit). We will compare the mean or median, as appropriate for distribution, for rTMS and sham groups at each time point, and the change between baseline MRI and post-intervention MRI metrics of sham and rTMS intervention groups, including metrics for whole brain, lobe-specific and lesion locations.Lesion analysis: number of new and number of enlarging T2 hyperintense lesions, combined volume of lesion(s) within each lobe.Atrophy analysis: normalised percentage brain volume change from baseline to post-intervention MRI timepoints will be estimated using SIENA [26], part of FSL [27]. For substructures, including white matter, grey matter, peripheral (cortical) grey matter and ventricular cerebrospinal fluid, SIENAX [26], part of FSL-FIRST [27] will be used to determine normalised tissue volumes at each timepoint.Diffusion tensor imaging (DTI) metrics: mean diffusivity, fractional anisotropy, axial diffusivity and radial diffusivity. Considered together, these metrics are indicative of axonal and myelin integrity.Magnetization transfer ratio (MTR) and quantitative T1 mapping (qT1, mean relaxation time) will be used to measure relatively subtle changes in myelin content [28].

DTI, MTR and qT1 metrics will be obtained for tissue types combined, and for each tissue type segmented into: white matter, grey matter, peripheral (cortical) grey matter and T2 lesional tissue.

*Symptom and quality of life assessments* will be collected at baseline (before the first intervention session), after the last intervention session, and again at remote follow-up (4 months after intervention allocation) will be used to compare change over time between rTMS and sham groups’ mean or median scores in assessments of:Anxiety and depression, using the Hospital Anxiety and Depression Scale (HADS) [29, 30].Overall quality of life, using the AQoL-8D’s health state utilities and dimensional scores [31].Fatigue, using the Fatigue Severity Scale (FSS) [30, 32].Cognitive and motor MS symptoms, using selected assessments from the Floodlight Open smartphone app test battery [33]. To assess cognitive symptoms, we will use number of correct matched pair responses within 90 s in the electronic Symbol Digit Modalities Test (e-SDMT). We will assess motor symptoms as upper limb manual dexterity using the Pinching Test (number of successful pinches within 30 sec) and Draw a Shape Test (tracing error as mean Hausdorff distance across all shapes); and as gait using the U-turn test (turn speed in radians per second, averaged across all U-turns made within the time period) [33].

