## Assignment of interventions: allocation

### Sequence generation {16a}

After confirming study eligibility, participant allocation to rTMS or sham will be performed automatically using REDCap software. We will use an allocation ratio of 2:1, with twice as many participants allocated to the active rTMS group as sham control, stratified by sex and a block size of 6.

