##### MRI

Proportion of participants with new lesions or enlarging lesions at the post-intervention time point will be compared between sham and rTMS using a Fisher’s exact test. Continuous MRI measures will be analysed with full factorial mixed MANOVA [within-subjects factor: time (baseline, post-treatment); between-subject factor: intervention group (rTMS, sham)], examining main effects and time*treatment interaction. If assumptions of MANOVA are violated when analysing combined MRI measures (e.g. items too highly correlated; Box’s test violated), we will split up the analyses into variable sets by tissue type and region (e.g. whole brain, lobe-specific measures separated). We may use deidentified data from publicly available MRI databases, including healthy control participants, in preliminary analyses to inform variable sets in multivariate analyses and to aid interpretation of results.

We will follow up MANOVA(s) with canonical discriminant analysis to examine rTMS/sham group separation on the linear combination of measures of myelin. We will also run univariate mixed-ANOVAs on measures of total myelin content, to examine the simple effects of intervention group at the post-intervention time point, as detailed a priori in the statistical analyses plan. False positives from multiple comparisons will be controlled using the false discovery rate (FDR) procedure [53] with threshold set at the conventional 5% level.

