##### Participant-reported questionnaire and Floodlight data

Continuous outcomes (AQol8D, HADS, FSS, U-Turn speed and Draw a Shape tracing error) will be compared between rTMS and sham conditions with univariate mixed-ANOVAs, as described above for MRI. Significant time by intervention interactions will be followed up with simple effects tests, comparing rTMS to sham group means within each time point.

Outcomes with count data (e-SDMT, Pinching, tracing error in the Draw a Shape test) will be analysed using Mann-Whitney *U* test to compare medians between rTMS and sham groups within each time point. The time by intervention interaction will also be examined using Mann-Whitney *U* tests on within-subject change from baseline, separately for the post-intervention and follow-up timepoints, controlling for false positives using FDR set at 5% threshold.

The statistical analyses carried out may be modified based on distributions observed and test assumptions. For all statistics, the level for significance will be set at *p*<0.05. Summary statistics will be prepared with means and standard deviations considered for normally distributed outcomes or median and interquartile range for non-normally distributed outcomes, as appropriate.

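### The lesion outcome is defined as counts of new and enlarging lesions, but the only named test is on the proportion of participants with such lesions; the cost depends on a lesion rate the protocol does not give

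*Protocol article*

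**What the plan says.** Under Outcomes {12}, Secondary outcomes, the MRI item lists the lesion measures as "Lesion analysis: number of new and number of enlarging T2 hyperintense lesions, combined volume of lesion(s) within each lobe". The general sentence before it, which applies to all MRI metrics, is "We will compare the mean or median, as appropriate for distribution, for rTMS and sham groups at each time point", together with the change from baseline. It names no test.

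Under Statistical methods {20a}, MRI, the lesion comparison is "Proportion of participants with new lesions or enlarging lesions at the post-intervention time point will be compared between sham and rTMS"; the method named is Fisher's exact test. The next sentence deals with the remaining MRI data: "Continuous MRI measures will be analysed with full factorial mixed MANOVA", with time (baseline, post-treatment) as the within-subject factor.

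Under Participant-reported questionnaire and Floodlight data, the protocol has a rule for counts, but it lists only smartphone outcomes: "Outcomes with count data (e-SDMT, Pinching, tracing error in the Draw a Shape test) will be analysed using Mann-Whitney" *U* tests. The same section fixes the level: "For all statistics, the level for significance will be set at" *p*<0.05. Sidedness is not stated.

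**The concern.** The outcome that is defined and the outcome that is tested are different quantities. The first is two counts per participant; the second is a yes/no status. Under the named test, a participant with one enlarged lesion and a participant with ten new lesions score the same, and a change in lesion number among people who have at least one lesion anyway cannot be seen.

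The yes/no version is itself not pinned down. The phrase joining new and enlarging lesions can mean one composite (either kind) or two separate outcomes, whereas the outcomes section keeps the two kinds apart. The methods section also allows analyses to be changed in the light of the distributions observed. With a count version, a composite version and a separate version all defensible from the text, the choice of result could be made after the data are seen.

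**Working it through.** **1. Does any named test reach the counts?**

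| Candidate | Covers counts of new or enlarging lesions? |
|---|---|
| Fisher's exact test (MRI) | No: proportion of participants |
| Mixed MANOVA (MRI) | No: continuous measures at two time points. Under Lesion assessment, a new lesion is one present after the intervention and absent at baseline, so the count has no baseline value. Lobe lesion volume can enter. |
| Mann-Whitney rule for counts | No: lists app outcomes only |
| Mean or median comparison (Outcomes) | A summary by group; no test named |

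So the stated test does not address the stated outcome.

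**2. What does it cost?** The protocol states no power, lesion rate or dispersion for this outcome, so there is no figure to reproduce. All means and dispersions below are assumptions.

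Inputs from the protocol:
- Arms 20:10 as planned (Abstract). At the 20 participants at which recruitment closed (Trial status), about 13:7, inferred from "We will use an allocation ratio of 2:1, with twice as many participants allocated to the active rTMS group as sham control".
- Level 0.05, taken as two-sided.
- Scan interval: 0 to 2 weeks before the first session, 4 to 5 weeks of sessions, 0 to 2 weeks after. This gives 4 to 2 + 5 + 2 = 9 weeks.
- Participants are stable and relapse free for 3 months (Eligibility criteria), so low counts are plausible.

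Model: negative binomial counts with mean m and shape k, so the probability of any lesion is 1 − (k/(k+m))^k; for Poisson counts it is 1 − e^(−m). Each cell gives the power of Fisher's test on any lesion, then of a permutation rank-sum test on the counts, from 800 simulated trials (Monte Carlo standard error at most √(0.25/800) = 1.8 points).

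| Sham mean | rTMS mean | k | 20:10 | 13:7 |
|---|---|---|---|---|
| 0.1 | 0.3 | 0.5 | 1.8% / 1.9% | 0.5% / 0.6% |
| 0.1 | 0.5 | 0.5 | 10.0% / 9.9% | 4.0% / 4.5% |
| 0.2 | 0.05 | 0.5 | 10.4% / 11.0% | 6.4% / 6.6% |
| 0.2 | 0.6 | 0.5 | 8.6% / 8.1% | 2.6% / 2.8% |
| 0.5 | 0.15 | 0.5 | 16.9% / 21.9% | 11.5% / 13.0% |
| 0.5 | 1.5 | 0.5 | 9.5% / 18.5% | 5.6% / 10.4% |
| 1 | 3 | 0.5 | 12.5% / 24.6% | 7.0% / 14.6% |
| 2 | 0.6 | 0.5 | 16.4% / 30.9% | 9.9% / 22.5% |
| 0.5 | 1.5 | Poisson | 50.9% / 67.8% | 31.8% / 47.6% |
| 1 | 3 | Poisson | 55.2% / 95.2% | 35.8% / 80.4% |
| 2 | 6 | Poisson | 13.1% / 99.6% | 4.9% / 97.6% |

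Exact check on the 0.5 versus 1.5 row (k = 0.5, 20:10). The any-lesion probabilities are 1 − (0.5/1.0)^0.5 = 0.293 and 1 − (0.5/2.0)^0.5 = 0.500. Summing the binomial probabilities of all tables that Fisher's test rejects gives 12.4%. The simulated 9.5% is therefore low, and the ratio there is 12.4/18.5 = 0.67 rather than one half. For 1 versus 3 the ratio is 12.5/24.6 = 0.51.

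With k = 1, 20:10 and a sex-stratified permutation rank test, power is 29% (Fisher) against 57% (rank) for rTMS 0.5 and sham 2, and 36% against 66% for rTMS 4 and sham 1. The type I error of the stratified test stayed at or below about 5%.

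**3. The size of the trial.** For 80% power against a sham proportion of 10%, Fisher's test needs an rTMS proportion of about 65% at 20:10 or 79% at 13:7. At low lesion rates the sample size, not the yes/no coding, is the main limit.

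**The case against.** The strongest reply is that a test for one exploratory imaging measure is ordinarily left to the statistical analysis plan, which the protocol announces, along with a separate MRI analysis plan. That would settle the matter if the protocol were silent. It is not: it names a test, for a quantity other than the one it defined. An unseen plan may already resolve this, which is a reason to treat the point as minor.

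A second reply is that a participant-level proportion is an ordinary summary of sparse counts. This stands in part. At the low rates plausible here the two tests behave almost alike, so a reader who infers that Fisher's test throws away much of its power whatever the lesion rate goes beyond the documents, which give no rate. At 13:7 with k = 1, means of 0.1 (rTMS) and 0.3 (sham) give 6.9% against 7.1%. One low-rate scenario (0.6 rTMS, 0.2 sham) gave 5% against 12% with a simple Mann-Whitney test; with a permutation reference distribution that gap falls back within 0 to 5 points.

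A reader might also infer that the counts are dropped from the trial or that lesion volume goes untested. Neither follows: the outcomes section still plans a mean or median comparison of MRI metrics, and the MANOVA can take volume. Nor does any safety decision rest on this test; safety is judged on adverse events.

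**Conclusion.** The mismatch holds on the text alone: the outcome is two counts per participant, the named test is on a proportion whose composition is ambiguous, and no named test covers the counts.

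The loss of power is conditional. Under assumed negative binomial counts it runs from nothing to about 5 points when means are about 0.1 to 0.6, where power is low with either test (about 22% or less at k = 0.5). When the arm means are around 0.5 and 1.5 or higher, Fisher's test has about half the power of a rank test or less, nearer two thirds at the lower edge. If counts are closer to Poisson, the loss at those means is 17 points or more at 20:10. In the scenarios examined the permutation rank test was never materially worse. Because the outcome is secondary and exploratory, this is a minor correction.

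**What to change.** In Statistical methods {20a}, MRI, replace the lesion sentence with one that matches the outcomes section: compare the number of new and, separately, the number of enlarging T2 lesions per participant between arms by an exact or permutation rank-sum test, and report the difference in mean counts with its confidence interval. This follows the Mann-Whitney rule the protocol already uses for other counts. Stratifying by sex, the randomisation factor, is optional. Keep the proportion with any new lesion and the proportion with any enlarging lesion as two descriptive lines, which also removes the ambiguity about a composite.

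The cost is one sentence. The lesion numbers are already produced by the MRI processing, the protocol says no intervention comparison had been analysed at submission, and the analysis plan is to be signed off before data lock, so the change could still be pre-specified at that point. The downside is small: if nearly every count is 0 or 1, the rank test gains little over Fisher's test.

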### Participant timeline {13}

#### Pre-screening

Participants will complete a preliminary screening questionnaire by phone and be provided with the information sheet. We will contact participants after 2 weeks to confirm interest in participation.

#### Screening and enrolment (visit 0)

We will collect demographic, medical and MS history data, and participants will be assessed using the EDSS [34] and undergo a physical exam. Medical history will be checked against the clinical records of each participant and eligibility confirmed by the clinical PI. Participants will also register for the Floodlight Open app and researchers will assist them to install the app and login, if needed. The baseline MRI will be scheduled, and the participant granted access to the baseline questionnaires on REDCap (Fig. 1).

**Fig. 1 Fig1:**
[figure not shown]
Schedule of enrolment, interventions and assessments

#### Baseline MRI

This will be performed ≤ 2 weeks before the first intervention visit*.*

#### Baseline questionnaires

After completing the MRI, participants will be asked (via email) to complete the baseline questionnaires and Floodlight Open app assessments. If baseline assessments were not completed remotely prior to intervention visit 1, these will be completed at visit 1 (prior to the intervention). Group will be allocated prior to the first intervention visit.

#### Intervention phase (visits 1–20) (~15min per day)

Upon arrival each day, participants will be asked to confirm their personal details (name and date of birth) and will be asked if they are experiencing any symptoms that are out of the ordinary. Participants will attend 20 sessions over a period of 4 consecutive weeks. A tolerance of +3 days will be allowed for weekends, sickness or inability to attend a session. Sessions will continue until 20 sessions are complete or up to a maximum of 5 weeks, whichever comes sooner. AEs and any concomitant medication changes will be recorded daily.

#### Blinding success survey (visits 1, 10 and 20)

Participants will be asked which intervention group they think they are in. If they select placebo or real, they will also complete a VAS to assess level of certainty and asked the reason(s) for their guess.

#### Visit 20 only

After the final intervention is conducted, participants will be asked to complete the post-intervention questionnaires (HADS, AQoL, FSS) and Roche Floodlight app assessments (~10 min to complete). Post-intervention MRI (~60 min) will coincide with visit 20, or within 2 weeks of visit 20. Acquisition sequence will be identical to baseline MRI.

#### Remote follow-up (visit 21) (~30–45min)

Questionnaire and Floodlight app assessments will be repeated at 4 months post-allocation and can be conducted remotely via phone with questionnaires returned via REDCap or post, if necessary.

### Sample size {14}

Thirty participants in total will be recruited. The sample size of 30 participants has been selected based on the safety and exploratory nature of the study.

### Recruitment {15}

Patients attending the MS Clinic at the Royal Hobart Hospital will be referred to researchers at the Menzies Institute for recruitment. Menzies researchers will obtain verbal consent to pre-screen participants using a phone screening questionnaire. Based on fulfilment of the eligibility criteria, participants will be sent the participant information sheet for consideration and invited to take part in the study. The participant information sheet will be provided by mail (or in person where practical). Follow-up phone calls will be made 2 weeks after providing documentation if the participant has not contacted the research team. Any questions regarding the study will be answered and their eligibility and agreement to take part confirmed.

Participants will also be recruited by promotion of the trial via the Menzies newsletter, webpage, social media pages or clinic posters/flyers, and local recruitment will be supported by patient advocacy groups such as MS Australia or MS Ltd.

## Assignment of interventions: allocation

### Sequence generation {16a}

After confirming study eligibility, participant allocation to rTMS or sham will be performed automatically using REDCap software. We will use an allocation ratio of 2:1, with twice as many participants allocated to the active rTMS group as sham control, stratified by sex and a block size of 6.

### Concealment mechanism {16b}

Because allocation is performed using REDCap’s randomisation software at the time of participant enrolment, there is no requirement to conceal an allocation sequence. REDCap is user access controlled to maintain blinding of blinded researchers.

### Implementation {16c}

Researchers delivering rTMS will enrol participants and perform randomised group allocation, the allocation sequence will be generated by the REDCap randomisation module. Researchers performing randomisation are necessarily un-blinded to perform the intervention.

## Assignment of interventions: blinding

### Who will be blinded {17a}

Participants will be blind to intervention assignment. MRI raw images will be assessed by blinded researchers. Statistical analyses will be deidentified but unblinded due to the uneven group allocation ratio (2:1); however, researchers performing the statistical analyses will not be involved in participant recruitment, allocation or delivery of the intervention. Researchers delivering rTMS/sham will be unblinded to the intervention group as sham is achieved by changing the orientation of the rTMS coil to prevent the magnetic field from entering the brain. Adverse event data will be collected by the researcher delivering the intervention at each intervention visit and is therefore, also unblinded. Adverse event data will be assessed and graded by the clinical PI who will remain blind to allocations.

### Procedure for unblinding if needed {17b}

It should not be necessary to break the intervention allocation code or unblind the participants during the study period. If necessary, request for un-blinding will be sent to the research PI or CI of the study, and if permission is granted, the allocation revealed. The unblinded researcher performing rTMS or the data manager will be able to access the allocations via the REDCap database software used for randomisation. Only at the end of the study will participants be informed of their allocation group, if requested.

Only after all data queries are resolved and the database is locked will the data be extracted for analysis and the intervention group coded in the dataset.

## Data collection and management

### Plans for assessment and collection of outcomes {18a}

#### Adverse events

AEs will be coded using the Medical Dictionary for Regulatory Activities (MedDRA), each AE will be counted once only for a given participant, presented by System Organ Class (SOC) and preferred term groupings. Details of any AEs will be collected using standardised case report forms and entered electronically into REDCap. The AE start date, stop date, severity, relationship, expectedness, outcome and duration will be recorded. To aid interpretation of AEs and secondary outcome measures, we will also collect data reporting concomitant medications or any changes to medications, recorded daily over the course of the intervention.

#### Protocol compliance

The number of sessions completed will be summed for each participant to assess the proportion of sham vs. rTMS participants that completed all 20 intervention sessions.

#### Blinding success

Participants will be asked by the researcher administering the intervention whether they think they are in the real or placebo (sham) group, or if they are unsure. We will also ask why participants think they are in this group, or why they are unsure, and responses will be entered by the researcher into the electronic case report form (eCRF). If participants select either the real or placebo option, they will also rate their level of certainty of this guess along a VAS by using a slider on a touchscreen from ‘very uncertain’ to ‘very certain’, which is then numerically scored. Successful blinding is defined as a high proportion of “unsure” responses and approximately equal proportion of responses across participant guesses, though participants’ awareness of the allocation ratio could bias guess choice [35]. Blinding will be considered unsuccessful if more than 60% of participants in the sham arm correctly identify their group and rate certainty of their selection in the top 25% of the scale, in line with recommendations from assessments of bias under various (un)blinding scenarios [36, 37]. Blinding success will be primarily assessed after the first intervention visit as this is less likely to be confounded by perceived efficacy of the intervention [38], in accordance with CONSORT 2010 guidelines, item 11 [39].

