### Secondary objectives

To determine if a 5 days per week treatment regime is feasible for people with MS.To determine if the sham protocol is sufficient to maintain participant blinding.To determine if there is any evidence that rTMS alters myelin addition as detected using MRI measurements, to warrant further analysis in a phase II efficacy trial.To explore if there is any benefit of rTMS to MS symptoms (anxiety and depression, quality of life, fatigue, cognition and motor symptoms).

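### The definition of successful blinding looks at how evenly the guess categories are used, not at whether guesses differ between arms, and even use is the wrong benchmark under 2:1 allocation

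*Protocol article*

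**What the plan says.** Blinding is a stated secondary objective: "To determine if the sham protocol is sufficient to maintain participant blinding" (Secondary objectives). The section on the choice of comparators adds that the result is meant to inform a phase II study. Participants answer real, placebo or unsure after sessions 1, 10 and 20, and session 1 is primary.

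The section Blinding success, under Plans for assessment and collection of outcomes {18a}, gives two rules:

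- Success: "Successful blinding is defined as a high proportion of “unsure” responses and approximately equal proportion of responses across participant guesses". The sentence continues: "though participants’ awareness of the allocation ratio could bias guess choice".
- Failure: "Blinding will be considered unsuccessful if more than 60% of participants in the sham arm correctly identify their group" and also "rate certainty of their selection in the top 25% of the scale".

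Allocation is unequal: "We will use an allocation ratio of 2:1, with twice as many participants allocated to the active rTMS group as sham control" (Sequence generation {16a}). The outcome and statistical methods sections report guesses by intervention group, descriptively.

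**The concern.** A trial is blinded when a participant's answer does not depend on the arm received. That implies the same distribution of answers in both arms. It does not imply that 'real' and 'placebo' are chosen equally often. The success definition tests the second condition and leaves out the first.

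Under 1:1 allocation the two conditions are close in practice. Under a known 2:1 ratio they separate, because a participant with no information about the arm can sensibly lean towards 'real'. The definition counts that against the sham. The protocol names the bias but leaves the criterion as it is.

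At stake is the verdict on whether this sham is good enough to carry forward. A label driven by the allocation ratio and by how often people say 'unsure' could mislead that decision in either direction.

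**Working it through.** The protocol gives no operating figure for the blinding criterion, so there is none to reproduce.

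**Inputs from the protocol article.** Planned arms 20 rTMS and 10 sham (Abstract; 2:1 in Sequence generation). Recruitment closed at 20 (Trial status), which is about 13:7 at 2:1; that split is an assumption. Three answer categories. Sham failure threshold above 60%.

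**Assumptions, because the protocol gives no values.** A blinded guesser says 'real' with probability 2/3. 'Approximately equal' means 'real' is within t = 10 or 20 points of 50% of guesses. 'High' means at least 50% unsure.

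**Step 1. Equality over all participants, perfect blinding.** With g guessers, P(miss) = 1 − Σ C(g,k)(2/3)^k(1/3)^(g−k), summed over k with |k/g − 0.5| ≤ t.

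| Guessers g | k allowed at ±10 | P(miss), ±10 | P(miss), ±20 |
|---|---|---|---|
| 30 | 12–18 | 0.73 | 0.29 |
| 20 | 8–12 | 0.67 | 0.30 |
| 15 | 6–9 | 0.63 | 0.41 |
| 10 | 4–6 | 0.58 | 0.30 |

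If the ratio has no influence (probability 1/2), P(miss) at ±10 is 0.20 to 0.34.

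**Step 2. Equality required within each arm.** P(miss) = 1 − (1 − m₁)(1 − m₂), where m₁ and m₂ are the arm-level values at ±10.

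- All guess (20 and 10): 1 − (1 − 0.665)(1 − 0.579) = 0.86.
- Half guess (10 and 5): 1 − (1 − 0.579)(1 − 0.506) = 0.79.
- At ±20 these become 0.51 and 0.66.

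**Step 3. The full success rule over all participants, 20/10, 60% unsure in each arm.** Guesser counts are Binomial(20, 0.4) and Binomial(10, 0.4). Success needs at least 50% unsure and 'real' between 40% and 60% of guesses.

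- Perfect blinding, P(real) = 2/3 in both arms: met in about 27% of trials.
- Every guess correct, P(real) = 1 in rTMS and 0 in sham: met in about 26%.

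The expected pooled split is the same in both cases. Twelve guessers at 2/3 give 8 'real' to 4 'placebo'; eight correct rTMS guessers and four correct sham guessers also give 8 to 4. The pooled split therefore carries almost no information on blinding.

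**Step 4. An all-correct outcome that meets the success definition and does not trigger the failure rule.**

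| | real | placebo | unsure |
|---|---|---|---|
| rTMS (20) | 6 | 0 | 14 |
| sham (10) | 0 | 6 | 4 |

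Unsure is 18/30 = 60% and the guesses split 6:6, so success is met. Sham correct is 6/10 = 60%, which is not more than 60%, so the failure rule is silent whatever the certainty scores. Yet all 12 guesses are right; Fisher's exact two-sided p among guessers is 2/C(12,6) = 2/924 = 0.002. At 13/7 the same happens with 4 'real', 4 'placebo' and 12 unsure: 60% unsure, a 4:4 split, and 4/7 = 57% of sham correct.

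**Step 5. A between-arm comparison on the same cases.** Under perfect blinding with 60% unsure, the share answering 'real' is 0.4 × 2/3 = 0.27 in each arm, a difference of 0. In the Step 4 table it is 6/20 − 0/10 = 30 points for 'real' and 0/20 − 6/10 = −60 points for 'placebo'.

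**Step 6. The sham failure rule under perfect blinding.** Take P(placebo) = 1/3, nobody unsure and everyone highly certain. It then triggers wrongly with P(X ≥ 7 | n = 10) = 0.020 or P(X ≥ 5 | n = 7) = 0.045.

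**The case against.** The strongest reply is that the equality clause is not the whole test. The next sentence of the protocol is specific to the sham arm, uses correctness and certainty, and does not require equal categories. Step 6 shows that perfect blinding rarely trips it, and it always fires if all sham participants are correct and highly certain. That stands, and the rule should stay. But it looks at one arm and only at confident guesses, so it does not supply the missing comparison.

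Two stronger readings are tempting, and the documents do not support them.

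- *That perfect blinding usually fails the definition.* This depends on cut-offs that the protocol does not give. In the Step 3 setting with ±20 points, a perfectly blinded 2:1 guesser passes in about 53% of trials. If guesses ignore the ratio, misses are much less frequent. Guessing at exactly 2/3 is itself an assumption; the protocol says only that awareness of the ratio could matter.
- *That unblinded guessing passes in general.* If everyone guesses and is right, nobody is unsure and the definition fails. An exactly even split needs sham participants to guess about twice as often as rTMS participants, which nothing in the protocol predicts. Within arms, all-correct guessing never passes, and guesses are to be tabulated by arm. With 7 or more of 10 sham correct, the failure rule would also fire if those seven were highly certain.

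It is also fair that reporting is descriptive, that no go/no-go rule is tied to the label, that the ratio bias is disclosed, and that the unseen statistical analysis plan may add an estimate. This limits the consequence. It does not repair a success definition that the protocol itself states.

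**Conclusion.** The point holds in a limited form. Without any numerical assumption, the definition of success does not compare arms, does not say whether equality is pooled or within arm, and names the 2:1 bias without adjusting for it. Outcomes can also fall between the two rules and be neither successful nor unsuccessful.

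The size depends on the assumptions listed in the working. Ratio-following guesses by blinded participants miss equality more often than not at ±10 points on either reading. At ±20 that remains so only within arms. The near-identical pass rates for blinded and unblinded guessing apply to the pooled reading alone.

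A reader might infer that the protocol has no usable check on unblinding, or that its verdict will be wrong. Neither follows, since the sham rule and the by-arm table both remain. The criterion should be changed, but this is a correction to a secondary objective and does not touch the primary safety outcome.

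**What to change.** Drop the clause on equal use of guess categories as the success criterion. In its place, estimate the difference between rTMS and sham in the proportion answering 'real', and likewise 'placebo', with all participants who gave an answer in the denominator and 'unsure' kept as its own category. Give an exact 95% confidence interval, primarily at session 1 and also at sessions 10 and 20. Judge blinding by how far the differences lie from zero. Keep the sham-arm rule on confident correct guesses alongside.

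The cost is about one sentence in the protocol or analysis plan and a few estimates from data already collected and tabulated by arm. The Trial status section says no intervention comparisons had been analysed at submission, so the change could be made before results are seen. The drawback is precision: with 20 to 30 participants the interval will be wide, so it should be reported as an estimate and not as proof that blinding held.
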